**Methods/Design:**

The MONET – study (***M***R mammography ***O***f ***N***onpalpable Br***E***ast ***T***umors) is a randomized controlled trial with diagnostic and therapeutic endpoints. We aim to include 500 patients with nonpalpable suspicious breast lesions who are referred for biopsy. With this number of patients, the expected 12% reduction in surgical procedures due to more accurate preoperative staging with Breast MRI can be detected with a high power (90%). The secondary outcome is the positive and negative predictive value of contrast enhanced Breast MRI. If the predictive values are deemed sufficiently close to those for large core biopsy then the latter, invasive, procedure could possibly be avoided in some women. The rationale, study design and the baseline characteristics of the first 100 included patients are described.

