### Interpretation of Breast MRI

MR images of the breast will be interpreted on soft copy using a Picture Archiving and Communications System (PACS, Philips, Best, The Netherlands) that allows manual window level setting. MR images will be interpreted by two radiologists independently and in case of discrepancy, consensus will be sought. The radiologists will have access to the mammograms and ultrasound examination, but will be blinded for the results of the LCNB, following clinical practice. The MR images will be interpreted following the guidelines of the BI-RADS-MRI classification system proposed by the American College of Radiology [18]. Classification of the lesions will be based on lesion morphology, enhancement pattern and enhancement kinetics (persistent, plateau, or washout) [19,20]. Level of suspicion will be reported on a scale of 0 – 6: 0 additional imaging required; 1 normal; 2 benign; 3 probably benign, 6-month follow-up MRI recommended; 4 suspicious for malignancy; 5 highly suggestive of malignancy; 6 known malignancy.

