### Secondary outcome

Previous studies have shown that the positive predictive value of nonpalpable, BI-RADS 5 lesions detected on mammography is 96% [21]. If these lesions are classified as BI-RADS-MRI 5 as well, we expect the positive predictive value to increase further. In the 250 women who will undergo Breast MRI (intervention group), the positive and negative predictive values of Breast MRI in combination with mammography and ultrasound will be determined. If the predictive values are high (in certain subgroups, e.g patients with microcalcifications and dense breast lesions on mammography), LCNB could be omitted in the future in some women. Since all patients in the MONET – study will undergo LCNB, following clinical practice, the number of patients in whom LCNB could possibly be omitted in the future will be estimated based on the calculated predictive values of the MRI.

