### Data-analysis

We will compare the number of all biopsies and surgical procedures within one year after the first LCNB between the MRI group and the control group. To compare the diagnostic performance of MRI (in combination with mammography and ultrasound) and LCNB, a two-by-two table will be constructed in which the results of breast MRI in addition to mammography and ultrasound will be compared to the results of the histology of the tissue sampled at the large core needle biopsy. The positive predictive value will be calculated by dividing the number of correctly identified positives by the total number of positive Breast MRI's. The negative predictive value will be calculated by dividing dividing the number of correctly identified negatives by the total number of negative MRI's. Analyses will be performed for specific subgroups, i.e. microcalcifications and dense breast lesions on mammography. If the positive predictive value of mammography, ultrasound and Breast MRI is sufficiently close the positive predictive value of large core needle biopsy in patients with nonpalpable breast lesions in all patients or in a subgroup of patients, the biopsy in these patients may be replaced by MRI in the future. However, whether MRI can indeed replace LCNB in clinical practice will have to be assessed in a separate study.

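### The single pooled two-by-two table does not calculate the mammography-by-MRI combination that the Secondary outcome section puts forward for omitting biopsy

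*Protocol article*

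**What the plan says.** The Abstract (Background) and the Background section state the aim of finding a subgroup in which the three imaging methods together settle the diagnosis.

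The index test is described in several ways:
- Abstract, Methods/Design: "The secondary outcome is the positive and negative predictive value of contrast enhanced Breast MRI".
- Secondary outcome: "the positive and negative predictive values of Breast MRI in combination with mammography and ultrasound will be determined". The same section later bases its estimate of omittable biopsies on predictive values attributed to the MRI.
- Data-analysis: "a two-by-two table will be constructed in which the results of breast MRI in addition to mammography and ultrasound will be compared" with core biopsy histology. The PPV comes from "dividing the number of correctly identified positives by the total number of positive Breast MRI's", and the negative predictive value (NPV) from dividing "the number of correctly identified negatives by the total number of negative MRI's". The conclusion starts from the three methods again: "If the positive predictive value of mammography, ultrasound and Breast MRI is sufficiently close" to that of biopsy.

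The Secondary outcome section gives a PPV of 96% for mammographic BI-RADS 5 and expects a higher value when the lesion is also BI-RADS 5 on MRI. The Data-analysis section names two subgroups, microcalcifications and dense lesions. The Secondary outcome section gives the same two as examples.

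**The concern.** The expectation in the Secondary outcome section is about a cell of a cross-classification: mammographic category 5 and MRI category 5. The stated analysis pools every positive MRI, whatever the mammographic category and whatever the degree of MRI suspicion. The two subgroups split lesions by mammographic appearance, not by BI-RADS category, so they do not recover that cell.

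At stake is whether the secondary outcome can answer its own question. A pooled PPV well below that of biopsy would read as a negative answer even if a small group existed in which the combination was nearly conclusive. The count of biopsies that might be omitted would also rest on an average over women in very different positions.

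**Working it through.** The article states no expected predictive value for MRI or for the combination, so there is no figure to reproduce. What follows is an illustration.

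**Inputs**
- Malignancy: 40 of 113 biopsy diagnoses = 35.4% (Preliminary results, Table 2).
- MRI sensitivity 0.90, specificity 0.72 (Background, meta-analysis).
- Mammographic BI-RADS 3/4/5: 45/47/11, so category 5 is 11 of 103 lesions with a known category (Table 2).
- PPV of mammographic BI-RADS 5: 96% (Secondary outcome).
- MRI group: 250 women, treated as one lesion each.
- Assumption not in the article: MRI and mammography are independent given disease.

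**Pooled table**
- Malignant: 250 × 40/113 = 88.5. Not malignant: 161.5.
- True positives 0.90 × 88.5 = 79.6; false positives 0.28 × 161.5 = 45.2. PPV = 79.6/124.9 = 63.8%.
- True negatives 0.72 × 161.5 = 116.3; false negatives 0.10 × 88.5 = 8.8. NPV = 116.3/125.1 = 92.9%.
- Over the 10% to 55% malignancy range in the Background section, the PPV runs from 26.3% to 79.7% and the NPV from 98.5% to 85.5%.

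**Mammographic BI-RADS 5 with a positive MRI**
- Women with mammographic BI-RADS 5: 250 × 11/103 = 26.7, of whom 0.96 × 26.7 = 25.6 have a malignant lesion and 1.1 do not.
- MRI positive: 0.90 × 25.6 = 23.1 true and 0.28 × 1.1 = 0.3 false, 23.4 in all.
- PPV = (0.90 × 0.96)/(0.90 × 0.96 + 0.28 × 0.04) = 0.864/0.8752 = 98.7%.

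**What pooling does**
- These 23.4 women are 23.4/124.9 = 19% of the pooled positives. The other 101.5 have a PPV of (79.6 − 23.1)/101.5 = 56%. The pooled 64% describes neither group.

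**Two limits**
- Most of the gap comes from the mammographic category. If MRI added nothing within BI-RADS 5, the PPV there would still be 96%. The gain from MRI in this illustration is 96% to 98.7%, and it can be seen only if the table is split by entry category.
- The article gives no MRI accuracy by category. The exact cell of interest, BI-RADS 5 on both, cannot be calculated; any positive MRI stands in for it.

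**The case against.** A reader might infer more: that the formula measures MRI alone and so gives the predictive value of a different test from the one in the conclusion. The article does not support that. The sentence before the formula builds the table on MRI in addition to mammography and ultrasound, so positive MRIs is naturally shorthand for the positive row of that table. The Interpretation of Breast MRI section says "The radiologists will have access to the mammograms and ultrasound examination", so the reading is made with conventional imaging in view. It also says "Classification of the lesions will be based on lesion morphology, enhancement pattern and enhancement kinetics", but that does not show that the readers ignore the other images. Every woman enters with BI-RADS 3 to 5 on mammography or ultrasound. At that threshold, positive on both MRI and conventional imaging is the same set as positive on MRI, with the same PPV of 63.8%.

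Nor does the 0 to 6 scale defeat a positive/negative split. Categories 1 to 5 are ordered and can be cut. The cut itself, and the place of categories 0 and 3, are details that a condensed article may leave to the full protocol.

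It can also be said that the BI-RADS 5 sentence is an expectation rather than an analysis definition, and that independence given disease is doubtful when readers see the mammogram. Both are fair. The second affects the 98.7%, but an informative MRI would not bring the PPV below the 96% that mammography gives by itself. The first does not explain why the analysis leaves out the one combination that the article singles out.

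**Conclusion.** The point holds in a limited form. The stated analysis does not calculate the combination that the Secondary outcome section puts forward, and the two named subgroups do not supply it. On the article's figures, with independence assumed, the contrast is a pooled PPV of about 64% (NPV about 93%) against about 99% for mammographic BI-RADS 5 with a positive MRI. That group comes from about 27 of 250 women before the MRI condition is applied. The pooled table could therefore miss the subgroup that the trial hopes to identify.

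The varying names for the index test are loose wording; the formula is not shown to be wrong. Severity is minor. The outcome is secondary, all women undergo core biopsy, and the Data-analysis section requires a separate study before MRI could replace it.

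**What to change.** Keep the pooled two-by-two table and add one prespecified table:
- Tabulate BI-RADS-MRI category against core biopsy histology, the reference the plan already states, crossed with the entry mammography/ultrasound BI-RADS category.
- Give the malignancy rate with a 95% confidence interval in each cell, including mammographic 5 with MRI 5, and the total for each entry category, so that the contribution of MRI is visible.
- Keep MRI category 0 in the denominator, counted as biopsy not avoidable.
- Base the estimate of potentially omittable biopsies on these category-specific rates.
- Use one name for the index test in the Abstract, Secondary outcome and Data-analysis sections.

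The data are already being collected, so the cost is wording and one larger table. The drawback is wide intervals in small cells. With 23 women in a cell and all 23 lesions malignant, the exact two-sided 95% lower limit is 0.025^(1/23) = 85%. The table would therefore indicate where a further study should look, without settling the question.

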### Study design

The MONET – study is a randomized controlled trial. Patients will be recruited in 3 hospitals: two large community teaching hospitals and one University Medical Center. In all participating centers, Breast MRI is not part of routine clinical practice in the work-up of patients with suspicious nonpalpable breast lesions. We aim to include a total of 500 patients with nonpalpable, mammographically suspicious breast lesions who are referred for biopsy. After giving informed consent, patients will be randomized in the control group or the MRI group. Patients in the control group (n = 250) will undergo routine medical care. This includes mammography, ultrasound, and the lesion is sampled by means of large core needle biopsy. In case of malignancy (DCIS or invasive carcinoma), the lesion is surgically removed. The MRI group (n = 250) will undergo routine clinical care and in addition, contrast enhanced Breast MRI in the University Medical Center prior to the large core needle biopsy. The MRI scan will be performed within one week after mammography and before LCNB which will be performed within one week after MRI to avoid a diagnostic delay.

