### LCNB

LCNB will be performed under ultrasound guidance or stereotactically. A minimum of four 14 Gauge biopsy specimens per lesion is acquired. The histological diagnosis of the tissue sampled by means of the LCNB provides the definitive diagnosis. Based on histology, patient management will be planned: 'benign lesions' require mammographic follow-up, 'normal breast tissue' requires a repeat LCNB or open breast biopsy and in case of a 'high risk lesion' (i.e. lobular carcinoma in situ, atypical ductal or lobular hyperplasia), 'in-situ carcinoma' or 'invasive carcinoma' require image-guided needle localization followed by surgical excision with appropriate axillary staging (i.e. sentinel node biopsy or axillary lymph node dissection). Patient management will be the same for the MRI and the control group.

If in the intervention group an additional, mammographically occult lesion is detected on the MR images that requires tissue sampling, second-look ultrasound will be performed to determine whether the lesion is ultrasonographically evident and suitable for ultrasound-guided tissue sampling. If the lesion cannot be visualised by means of second-look ultrasound, MRI-guided large core needle biopsy will be performed.

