## Preliminary results

Between January 2006 and November 2006, 174 patients were eligible for the MONET – study. 108 patients were included in the study (recruitment rate 62%). The reasons for non-participation are listed in Table 1. Eight patients were excluded after randomization (no available histology (n = 5), unanticipated obesity (n = 1), technical failure of MR scanner (n = 1), age over 75 years (n = 1)). Three of the excluded patients were randomized in the control group and 5 in the MRI group. The characteristics of the 100 patients included so far in the MONET – study are summarized in Table 2. The mean age was 56.1 years (range 39.9 – 75.0 years). In these patients, a total of 109 lesions were detected: 108 lesions were detected on mammography and 1 lesion on ultrasound imaging. The majority of the lesions were microcalcifications and classified as BI-RADS 3 or 4. The histological diagnosis of the lesions included 2 non-representative, 9 normal breast tissue, 62 benign lesions, 21 non-invasive carcinomas and 19 invasive carcinomas. So, 35.4% of lesions turned out to be malignant (non-invasive and invasive) after LCNB. Forty-five patients were randomized into the MRI group and 55 into the control group.

**Table 1 T1:** Reasons for non-participation

**Reason non-participation**	**Number of patients (%)**
Unable to lie in prone position	1 (1.5%)
Metal implants	6 (9.0%)
Severe obesity	1 (1.5%)
Claustrophobia	16 (24.0%)
Geographical distance from teaching hospital to MRI too long	18 (27.0%)
Clinical indication for MRI of the breast	1 (1.5%)
Personal reasons	23 (35.0%)
**Total**	**66**

**Table 2 T2:** Characteristics of the first 100 patients included in the MONET – study

n	**100**
Referred from University Medical Center	**30**
Mean age (*range*)	**56.1 **(*39.9 – 75.0*)
Number of lesions detected on mammography	**108**
*density only*	*41*
*microcalcifications only*	*54*
*both*	*9*
*other*	*2*
*unknown*	*2*
BI-RADS classification mammography	
*3*	*45*
*4*	*47*
*5*	*11*
*unknown*	*5*
Number of lesions detected on ultrasound (*mammographically occult lesions*)	**1**
BI-RADS classification ultrasound	
*3*	*1*
*4*	*-*
*5*	*-*
*unknown*	*-*
Diagnosis LCNB	**113***
*non-representative*	*2 (1.7%)*
*normal breast tissue*	*9 (8.0%)*
*benign*	*62 (54.9%)*
*non-invasive carcinoma*	*21 (18.6%)*
*invasive carcinoma*	*19 (16.8%)*

* 4 lesions were sampled twice because of inconclusive results

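### The predictive-value analysis gives no place to high-risk biopsy results that the protocol sends to excision; if they are scored as negatives, the NPV overstates how many biopsies could be omitted

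*Protocol article*

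**What the plan says.** Four parts of the protocol article bear on this.

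- **LCNB.** Histology is sorted into classes that determine management. Benign lesions go to mammographic follow-up. Normal tissue leads to a repeat LCNB or an open biopsy. A separate class is introduced with "in case of a 'high risk lesion' (i.e. lobular carcinoma in situ, atypical ductal or lobular hyperplasia". It shares a branch with in-situ and invasive carcinoma, namely "image-guided needle localization followed by surgical excision with appropriate axillary staging".
- **Study design and Preliminary results.** The outline of routine care explains malignancy in brackets: "In case of malignancy (DCIS or invasive carcinoma), the lesion is surgically removed". The Preliminary results likewise count only non-invasive and invasive carcinoma as malignant (35.4%).
- **Data-analysis.** MRI, read together with mammography and ultrasound, is set against LCNB histology in a two-by-two table. The NPV divides "the number of correctly identified negatives by the total number of negative MRI's". The section does not assign the histological classes to the positive or negative side.
- **Secondary outcome.** The values obtained for MRI are then put to use; the sentence, cut before its last word, reads: "the number of patients in whom LCNB could possibly be omitted in the future will be estimated based on the calculated predictive values of the". The Abstract also ties both predictive values to avoiding biopsy.

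The results tabulated so far are "2 non-representative, 9 normal breast tissue, 62 benign lesions, 21 non-invasive carcinomas and 19 invasive carcinomas".

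**The concern.** A two-by-two table needs every biopsy result on one side or the other. Under the article's only definition of malignancy, a high-risk result falls on the negative side. Take a woman with a BI-RADS-MRI 2 reading whose LCNB shows atypical ductal hyperplasia. She would count as a correct negative, although under the LCNB section her biopsy is what led to surgery. With a BI-RADS-MRI 4 reading and the same histology she would count as a false positive.

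For the question whether MRI can recognise malignancy, this scoring is acceptable. For the question in whom LCNB could be left out, it is not. A biopsy whose result takes a woman to excision was not dispensable, yet the count of avoidable biopsies would include it. The estimate that answers the secondary question would then lean towards omission on the NPV side.

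**Working it through.** **Plan's own figure.** The LCNB rows of Table 2 give 2 + 9 + 62 + 21 + 19 = 113, the stated total. Malignant share = (21 + 19)/113 = 40/113 = 35.4%, as printed. The denominator is samplings, not lesions (109 lesions, four sampled twice; 40/109 would be 36.7%). Because the five rows use up all 113 results, none is left for a high-risk class. Elsewhere the same table marks empty classes with a dash.

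**Inputs from the article.** Sensitivity 0.90 and specificity 0.72 of breast MRI (Background); malignant share p = 40/113 = 0.354 (Preliminary results).

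**Assumed inputs, not in the article.** h = share of LCNB results that are high-risk, taken out of the non-malignant results. q = probability that MRI is negative on such a lesion. q = 0.72 treats these lesions like other non-malignant ones; q = 0.50 is a less unfavourable alternative.

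**Formulas, per LCNB result.**

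- Malignant and MRI-negative: 0.10p = 0.0354
- Other non-malignant and MRI-negative: 0.72(1 − p − h)
- High-risk and MRI-negative: hq
- All MRI-negative: N = 0.0354 + 0.72(1 − p − h) + hq
- NPV for malignancy (high-risk scored negative): [0.72(1 − p − h) + hq]/N
- NPV for no excision-requiring result (high-risk scored positive): 0.72(1 − p − h)/N
- The two differ by hq/N.

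**Without high-risk results (h = 0).** N = 0.0354 + 0.4651 = 0.5005, so NPV = 0.4651/0.5005 = 0.929.

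**Worked case, h = 0.05 and q = 0.72.** 0.72 × (1 − 0.354 − 0.05) = 0.4291 and hq = 0.0360, so N = 0.5005. NPV for malignancy = (0.4291 + 0.0360)/0.5005 = 0.929. NPV for excision = 0.4291/0.5005 = 0.857.

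| h | NPV, malignancy (q = 0.72) | NPV, excision (q = 0.72) | NPV, malignancy (q = 0.50) | NPV, excision (q = 0.50) |
|---|---|---|---|---|
| 3% | 0.929 | 0.886 | 0.928 | 0.898 |
| 5% | 0.929 | 0.857 | 0.928 | 0.877 |
| 8% | 0.929 | 0.814 | 0.927 | 0.844 |

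At q = 0.72 the gap is 0.72h/0.5005, or about 1.4 NPV points for each percentage point of high-risk share.

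**PPV, h = 0.05 and q = 0.72.** All MRI-positive = 1 − 0.5005 = 0.4995; malignant and MRI-positive = 0.90p = 0.3186. PPV for malignancy = 0.3186/0.4995 = 0.638. Scoring high-risk as positive adds 0.05 × 0.28 = 0.0140, giving 0.3326/0.4995 = 0.666.

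**In counts.** With 113 results per 100 women, the 250 women in the MRI group give about 282.5 results, of which 141 are MRI-negative. Of these, 10 are malignant. Adding high-risk results at q = 0.72 (282.5 × hq = 6.1, 10.2, 16.3), the excision-requiring results among MRI-negatives become about 16, 20 or 26 for h = 3%, 5% or 8%.

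**The case against.** The strongest reply is that the Data-analysis section never defines the reference-positive class. Scoring high-risk results as negative is inferred from the care outline and from a descriptive count, and a condensed article may leave the rule to a fuller document. The first half stands: the scoring is implied, not written. The second half goes only so far. The article itself fixes the formulas, the reference standard, the management classes and the meaning of malignancy, and it publishes coded results. The point is that these parts do not fit together for the biopsy question.

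Three further replies stand in full.

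- An NPV for malignancy on LCNB is a legitimate quantity, and nothing in its formula is miscalculated.
- The closing replacement criterion in the Data-analysis section names the PPV. Scoring high-risk results as negative lowers the PPV, which counts against omission. The NPV matters through the Abstract and the Secondary outcome section.
- The size rests on h and q, which the article does not give. The 0.90 and 0.72 describe MRI in general, not MRI combined with mammography and ultrasound, and the 113 results include repeat samplings.

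A reader might infer that Table 2 proves high-risk lesions were filed as benign. It does not. There may have been none, or lobular carcinoma in situ may have been entered under non-invasive carcinoma, where it would count as positive. The dashes for empty classes make a silently dropped zero row less likely, but they do not exclude it.

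A reader might also infer that the Study design and LCNB sections contradict each other on who is operated on. They do not. The first says malignant lesions are removed, without saying that others are not; the second gives the detail.

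**Conclusion.** The concern holds in a conditional form. The article's definition of malignancy leaves out a biopsy class that its own pathway excises, and neither the two-by-two table nor Table 2 gives that class a place. If it is scored as negative, the NPV remains valid for malignancy but overstates how many biopsies could be omitted, while the PPV is lower than under the excision-based scoring. For any non-zero share of high-risk results with some chance of a negative MRI, the NPV effect runs in that direction.

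The size is unknown. Under the stated assumptions the gap is about 4, 7 or 12 NPV points at shares of 3%, 5% or 8% with q = 0.72, and 3, 5 or 8 points with q = 0.50. It is zero if no high-risk results occur or if all are coded as non-invasive carcinoma. The documents do not support a claim that the NPV is certainly inflated, or that the secondary conclusion as a whole is biased towards omission.

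The consequence is bounded. This is a secondary outcome, all trial patients are to have LCNB, and the article leaves actual replacement of biopsy to a separate study. The point is still worth settling, because the estimate of avoidable biopsies is what such a study would build on.

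**What to change.** 1. Code high-risk as its own LCNB category and give it a separate row in Table 2, so that lobular carcinoma in situ and atypical hyperplasia sit neither under benign nor under non-invasive carcinoma. Show the row even if it is empty.
2. In Data-analysis, keep PPV and NPV for malignancy, stating that the reference-positive class is DCIS or invasive carcinoma.
3. Report beside them PPV and NPV with any LCNB result for which the LCNB section requires excision (high-risk, in-situ or invasive) as reference-positive. Use this version for the estimate of avoidable biopsies in the Secondary outcome section.
4. Score lesions whose sample shows normal or non-representative tissue by the repeat histology, since such a first result does not settle the diagnosis.

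The cost is one extra category in histology already collected, a second two-by-two table, and possibly a less favourable NPV. No additional patients, procedures or readings are needed, and no change to clinical management is implied.
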